### Outcomes

#### Primary outcome

The primary outcome will be the proportion of residents with Guideline concordant use of antipsychotics, benzodiazepines and antidepressants measured at the RACF-level. This outcome will be measured at the 6-month time point, informed by a similar study conducted in RACFs [42]. This overall Guideline concordance will be measured as a dichotomous outcome (i.e. concordant vs not concordant among those using the reference medication) (Additional file 2). This trial-specific composite outcome has been developed from a series of indicators for each medication contexts and developed by New South Wales Therapeutic Advisory Group.

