## Background

Persistent high rates of psychotropic medication use in residential aged care facilities (RACFs) remain a concern for residents, caregivers and other stakeholders. This is despite a lack of evidence supporting benefits of psychotropic medication but well-documented risks of harm. More than 60% of Australian RACF residents use regular psychotropic medications, with 41% prescribed antidepressants, 22% antipsychotics and 22% benzodiazepines on a regular basis [1]. Psychotropic medication prevalence is also highly variable, with a study across 27 RACFs in the state of Victoria reporting antipsychotic prevalence ranged from 0 to 95% (mean 32%) and antidepressant prevalence ranged from 10 to 89% (mean 48%) [2].

The American Psychiatric Association [3], European Academy of Neurology [4] and Australian Clinical Practice Guidelines and Principles of Care for People with Dementia [5] recommend avoiding antipsychotics in people living with dementia. Evidence suggests antipsychotics are associated with increased risk of cardiovascular and cerebrovascular events, falls and death [6, 7]. Benzodiazepines are associated with minimal and short-term improvements in sleep disturbances but also with an increased risk of hip fracture [8] and falls [9]. Antidepressants have uncertain benefits in people living with dementia and have been associated with adverse events including dry mouth, dizziness and falls [10].

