#### RACF Guideline concordance

Trained nurses and health or care professionals will assess Guideline concordance using a standard data collection form completed online (preferred) or in a paper-based version. The data collection form will include questions to assess concordance with indicators for each medication context (Tables 5, 6 and 7). This will require trained nurses and health or care professionals at each participating aged care provider organisation to assign each resident a unique trial identification number. Each aged care provider organisation will securely store the spreadsheet of each resident’s trial identification number, and this will only be accessed by appropriate staff employed by the aged care provider organisation, as needed for care delivery. The Project Management Team will not have access to this information and will not be able to identify residents.

**Table 5 Tab5:** Indicators to assess aggregate RACF-level concordance: antipsychotics

	***Indicators to assess aggregate RACF-level concordance***	***Corresponding Guideline recommendations***
1	Residents using antipsychotics have documentation of experiencing distressing psychotic symptoms and/or aggression/agitation within the past 12 weeks that represents a direct threat to either the resident or other residents, staff, or family for the resident’s prescription of the antipsychotic	GPS 9; CR 3
2	Residents using antipsychotics have documentation of individually targeted non-pharmacological management strategies to manage distressing psychotic symptoms and/or aggression/agitation that are currently in place	GPS 6
3	Residents using antipsychotics are using a second-generation antipsychotic	CR 1
4	Residents using antipsychotics have documentation of informed consent for use of the antipsychotic	GPS 8
5	Residents using antipsychotics have a documented date of next review for antipsychotic treatment effectiveness	GPS 10
6	Residents using antipsychotics have a current antipsychotic adverse event monitoring protocol in place	GPS 20
7	Residents using antipsychotics have used the current antipsychotic for less than 12 weeks	GPS 19; GPS 21
8	Residents using antipsychotics for more than 12 weeks are currently having the antipsychotic dose tapered	GPS 19; GPS 23

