9	Residents using antipsychotics for more than 12 weeks and not currently tapering have documentation that the resident has been reviewed by either a psychiatrist or geriatrician, a formal documented discussion between the prescriber and a psychiatrist or geriatrician in which both practitioners agree or a documented clinical review involving the prescriber and at least one other medical practitioner in which both practitioners agree	GPS 19; GPS 21; GPS 22

Abbreviations: *RACF*, residential aged care facility; *GPS*, good practice statement; *CR*, conditional recommendation. GPS and CR refer to those in the Clinical Practice Guidelines for the Appropriate Use of Psychotropic Medications in People Living with Dementia and in Residential Aged Care

**Table 6 Tab6:** Indicators to assess aggregate RACF-level concordance: benzodiazepines for sleep disturbance

	***Indicators to assess aggregate RACF-level concordance***	***Corresponding Guideline recommendations***
1	Residents using benzodiazepines have documentation of individually targeted non-pharmacological management strategies for sleep disturbance that were trialled for an adequate period of time prior to commencing the benzodiazepine	GPS 26
2	Residents using benzodiazepines have documentation of individually targeted non-pharmacological management strategies to manage sleep disturbance that are currently in place	GPS 6
3	Residents using benzodiazepines have documentation of informed consent for use of the benzodiazepine	GPS 8
4	Residents using benzodiazepines have a documented date of next review for benzodiazepine treatment effectiveness	GPS 10
5	Residents using benzodiazepines have a current benzodiazepine adverse event monitoring protocol in place	GPS 28
6	Residents using benzodiazepines have used the current benzodiazepine for less than 2 weeks	GPS 26
7	Residents using benzodiazepines for more than 2 weeks are currently having the benzodiazepine dose tapered	GPS 29
8	Residents using benzodiazepines for more than 2 weeks and not currently tapering have documentation of a review of the harms and benefits of benzodiazepine continuation	CR 6

*Abbreviations*: *RACF*, residential aged care facility; *GPS*, good practice statement; *CR*, conditional recommendation. GPS and CR refer to those in the Clinical Practice Guidelines for the Appropriate Use of Psychotropic Medications in People Living with Dementia and in Residential Aged Care

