**Table 7 Tab7:** Indicators to assess aggregate RACF-level concordance: antidepressants

	***Indicators to assess aggregate RACF-level concordance***	***Corresponding Guideline recommendations***
1	Residents using antidepressants have documentation of moderate or severe major depressive disorder	CR 9
2	Residents using antidepressants have documentation of individually targeted non-pharmacological management strategies that are currently in place	GPS 6
3	Residents using antidepressants have documentation of informed consent for use of the antidepressant	GPS 8
4	Residents using antidepressants have a documented date of next review for antidepressant treatment effectiveness	GPS 10
5	Residents using antidepressants have a current antidepressant adverse event monitoring protocol in place	GPS 36
6	Residents using antidepressants have used the current antidepressant for less than 6 months	CR 11
7	Residents using antidepressants for more than 6 months are currently having the antidepressant dose tapered	GPS 37
8	Residents using antidepressants for more than 6 months and not currently tapering have documentation of a review of the harms and benefits of antidepressants continuation	CR 11

*Abbreviations*: *RACF*, residential aged care facility; *GPS*, good practice statement; *CR*, conditional recommendation. GPS and CR refer to those in the Clinical Practice Guidelines for the Appropriate Use of Psychotropic Medications in People Living with Dementia and in Residential Aged Care

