### Sample size and power

The sample size of 19 RACFs was deemed to have sufficient statistical power. To estimate the statistical power of the helix, counterbalanced, three-strategy, and three-context area (medication type) trial design, we performed 1000 Monte Carlo simulations using Stata/SE Statistical Software: Release 17.0 (StataCorp. 2021). The sample size analysis was conducted at the RACF level based on the primary outcome (i.e. proportion of RACF-level Guideline concordant use of antipsychotics, benzodiazepines and antidepressants). The sample size was based on conducting analysis using a linear mixed model employing fixed, categorical factors for medication type and guideline implementation strategy and RACF as a random intercept. We assumed a minimum important effect size of an absolute change in the proportion of concordant medication category takers of 5% for the level 2 strategy relative to level 1 strategy and of 15% for the level 3 strategy relative to level 1 strategy. Given these assumptions, our sample size of 19 RACFs provides > 99% power to detect the absolute change in proportion of concordant medication category takers of 15% and 81% power to detect the absolute change in proportion of 5%.

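### The 6-month primary proportion is taken among current users of the drug class, so stopping or starting a drug can move it in either direction with no change in the care of those still using it

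*Protocol article*

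**What the plan says.** Three places in the protocol article agree on the denominator. Primary outcome scores each resident as "concordant vs not concordant among those using the reference medication". The Abstract describes concordance among people using the three classes. Sample size and power works with "an absolute change in the proportion of concordant medication category takers". On timing, Primary outcome states: "This outcome will be measured at the 6-month time point".

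Tables 5 to 7, under RACF Guideline concordance, list the indicators, and every one refers to residents using the drug. They include short duration ("Residents using antipsychotics have used the current antipsychotic for less than 12 weeks") and a taper in progress ("Residents using antipsychotics for more than 12 weeks are currently having the antipsychotic dose tapered"), with matching taper items for the other classes ("Residents using benzodiazepines for more than 2 weeks are currently having the benzodiazepine dose tapered"; "Residents using antidepressants for more than 6 months are currently having the antidepressant dose tapered"). None credits a completed stop. How the indicators combine is left to Additional file 2, which is not shown.

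The Level 2 section and Table 2 include sessions on initiation and discontinuation. The Level 3 section bases quarterly action plans on the trial indicators. Use of each class is itself a secondary outcome. A closing sentence under Secondary outcomes sets all residents present at each time point as the denominator for a list that includes the same concordance measure at 3, 9 and 12 months.

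**The concern.** Randomisation makes the residents of the RACFs comparable across strategy levels within a drug class. It does not make the users at month 6 comparable if the strategies change who uses the drug. The primary contrast (level 3 against levels 1 and 2) is then made in a group selected after randomisation. Part of any difference may come from who left or joined that group and not from better care of those in it.

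Both errors are possible. A strategy that completes tapers loses residents who may have been scored as concordant. A strategy under which non-concordant users stop gains points although nothing changed for the remaining users. New short-course users also enter and can meet the duration indicator. The economic measure, cost per additional resident who becomes concordant, inherits the problem if it uses the same definition, because a resident who stops is then not counted.

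**Working it through.** **The plan's own figures.** The article states 81% power for 5 points and over 99% for 15 points with 19 RACFs. The residual SD and alpha are not given, so the simulation cannot be rebuilt. As a consistency check, assume two-sided alpha 0.05 and a within-RACF contrast with SE = SD × √(2/19). Then 81% power at 5 points implies SD = 0.05 / [(1.960 + 0.878) × 0.3244] = 0.054, and that SD gives over 99.9% at 15 points. The two figures agree with each other. The 5- and 15-point effects serve below only as a yardstick.

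**Formula.** Let P be concordance among users before anyone stops, r the share of users who stop, and q the share of stoppers who were concordant. After stopping:

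P′ = (P − r·q) / (1 − r), so the shift is −r(q − P) / (1 − r).

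The score falls when q > P, rises when q < P, and is unchanged when q = P.

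**Example.** Assume an RACF of 100 residents. Background gives 22% regular antipsychotic use nationally, hence 22 users. Assume 11 are concordant and the number of residents stays at 100.

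| State | Among users (primary) | Concordant, of all residents | Non-concordant use, of all residents |
|---|---|---|---|
| Start | 11/22 = 50.0% | 11% | 11% |
| Five concordant users stop | 6/17 = 35.3% | 6% | 11% |
| Five non-concordant users stop | 11/17 = 64.7% | 11% | 6% |
| Five concordant new users start | 16/27 = 59.3% | 16% | 11% |
| Five non-concordant new users start | 11/27 = 40.7% | 11% | 16% |

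Stopping alone moves the primary score by 14.7 points either way. The third column shows that the all-resident denominator under Secondary outcomes does not help: a concordant user who stops still lowers that figure, and a non-concordant user who stops leaves it unchanged. The last column moves only when the number of residents with non-concordant use changes.

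**Range.** At P = 50%:

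- r = 10%: from +5.6 points (q = 0) to −5.6 (q = 100%).
- r = 20%: from +12.5 to −12.5.
- r = 44%: +15.7 if q = 30%, −15.7 if q = 70%. The Discussion cites a 44% reduction in antipsychotic use at 6 months from another pharmacist-led intervention.

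The excess q − P that would cancel a true effect d is d(1 − r)/r. At r = 44% this is 6.4 points for d = 5 and 19.1 for d = 15; at r = 20% it is 20 and 60 points.

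These are shifts in one RACF-by-context value. The bias in the strategy contrast is the difference in average shift between levels. It is near zero if stopping and starting are alike at all levels, and equals the full shift if they occur at one level only.

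**Empty contexts.** With no users of a class, the value is 0/0. The model takes one value per RACF and context, so only that value is lost; the RACF still contributes its other two.

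**The case against.** The strongest case is that concordance among users is a deliberate and coherent choice. The stated objective is to put the Guidelines into practice, not to reduce use, and use is reported separately at the same 6-month point. This stands as a reason to keep the primary outcome. It does not remove the problem: a prevalence figure alone does not show whether the use that disappeared was concordant. Multiplying prevalence by (1 − concordance) only approximates the missing quantity, because prevalence covers all indications while the Abstract limits the composite to changed behaviours.

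The sizes above rest on chosen scenarios, and this also stands. Whether a taper or short course makes a resident concordant depends on the unseen scoring file, and the tables list several other indicators. If the education topics run in the listed order, discontinuation is the fourth session, at 9 months, after the primary time point. Stopping before month 6 would then come from the level 3 action plans, the distributed materials and the initiation session. That may make it smaller, but it may still differ by level.

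A reader might infer that the knowledge broker strategy will look worse than it is. The documents do not support that, because the direction depends on who stops and who starts. A reader might also infer that an RACF without users drops out of the trial. It does not; it lacks one context value. Background does say "antipsychotic prevalence ranged from 0 to 95" per cent, but in a separate study of 27 RACFs with a mean of 32%, so how often empty contexts would arise here is unknown.

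**Conclusion.** The point holds as a matter of interpretation. The article fixes the denominator as users at 6 months, the strategies can change that group after randomisation, and no indicator credits a completed stop. The score can therefore shift with no change in the care of remaining users, in either direction. In the example, five of 22 users stopping is worth 14.7 points, about the whole 15-point target effect and nearly three times the 5-point one. This rests on assumed values of P, q and r, and on the composite being satisfiable by a resident who is tapering or on a short course. The documents show neither a net direction nor that bias of this size will occur. They do not show that the primary outcome is invalid. The two denominators given for the same concordance measure at different time points are a separate inconsistency in the text.

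**What to change.** Keep the primary outcome and make three changes.

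1. Pre-specify as a key supporting analysis, in the same mixed model at 6 months, the proportion of all residents with non-concordant use of each class. Non-users count as not having non-concordant use, so the value is defined wherever there are residents.
2. Show the number of users by strategy level and context beside each primary estimate, and interpret the primary result alongside the supporting one. Add no success condition: requiring both to improve would still call a strategy unsuccessful where completed tapers lowered the user-level score, and no power was simulated for it.
3. State under Secondary outcomes which denominator applies to concordance at 3, 9 and 12 months, so that it can be read with the 6-month figure.

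The cost is one more analysis of data already collected and a second figure, which may disagree with the primary. Effects on the all-resident scale are smaller and vary with use: 15 points among 22 users per 100 residents is 0.15 × 22 = 3.3 per 100, and among 41 antidepressant users 0.15 × 41 = 6.2 per 100. The supporting result should therefore be read by its estimate and interval.

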#### Secondary outcomes

Secondary outcomes will include:Proportion of residents with Guideline concordant use of antipsychotics, benzodiazepines and antidepressants measured at the RACF-level at 3-, 9- and 12-month time points. The 9- and 12-month time points will be used to evaluate intervention sustainability and will be useful for assessing policy and practice change that did not occur at the 6-month time point.Proportion of residents concordant with each individual indicator of the Guideline concordance composite outcome for antipsychotics, benzodiazepines and antidepressants use, measured at the RACF level at 3-, 6-, 9- and 12-month time points (Tables 5, 6 and 7).Proportion of residents using psychotropic medications (antipsychotics, antidepressants, benzodiazepines, z-drugs, opioids and anticonvulsants) measured at the RACF level at 3-, 6-, 9- and 12-month time pointsProportion of residents with hospitalisation, falls, falls with major injury, polypharmacy, quality of life and activities of daily living measured at the RACF level at 3-, 6-, 9- and 12-month time pointsProportion of residents with medication incidents and behavioural incidents measured at the RACF level at 3-, 6-, 9- and 12-month time pointsThese proportions will be calculated using the total number of residents at each RACF at each of the time points as a denominator.

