### Intervention

All three levels of implementation strategies will be delivered simultaneously throughout the 12-month intervention period at the RACF-level. Each level of implementation strategy includes the activities of the previous level (Table 1). Education resources will be provided to support knowledge brokers to deliver level 1 and level 2 implementation strategies. Level 3 implementation strategies will be customised to each RACF based on ongoing local needs assessments conducted by the knowledge broker.

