#### Level 2: Pharmacist-led QUM education activities

The level 2 strategy will involve provision of QUM services and distribution of the Guidelines and supporting materials. QUM services are Australian government-funded pharmacist-led group education activities [30]. The QUM service used in this trial will be developed to align with the Pharmaceutical Society of Australia Guidelines for QUM services and the Guidelines [30]. The QUM service will involve a face-to-face, online or pre-recorded group education activity delivered by an on-site aged care pharmacist, delivered to RACF registered nurses and enrolled nurses and aged care workers directly employed by the aged care provider organisation. Each QUM session will run for up to 70 min. The pharmacist will deliver a QUM service once per quarter, with a total of four QUM services delivered over the 12 months. The four sessions will cover the Guidelines, initiation, adverse events and monitoring and discontinuation relevant to the RACFs’ allocated medication context (Table 2).

**Table 2 Tab2:** Overview of QUM service to RACFs

		**Overview**	**Key take-home messages**
**Guideline introduction**		Introduction to the Guidelines, including the companion guide, medication factsheets and curated inventory of existing resources	Understand the background of the Guidelines, terminology used within the Guidelines and scope of the Guidelines
**Education activity**	Initiation	Each education activity will begin with a brief overview on the use of the psychotropic medication in people living with dementia and changed behaviours Attendees will work through a case study in small groups. Attendees will present their case study answers, and the facilitator will support group discussion. The facilitator will end the education activity with a brief conclusion of the key take-home messages Each component of the education activity will include interactive components to promote group discussion	The *initiation* education activity takes staff through the risks and benefits of the psychotropic medication for people living with dementia. It teaches nurses and aged care staff the steps they should take prior to considering initiation of the psychotropic medication
	Adverse events and monitoring		The *adverse events and monitoring* education activity reviews some key adverse events of the psychotropic medication and teaches nurses and aged care staff monitoring requirements for the psychotropic medication

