	*Intervention*: Delivery of knowledge broker services as per local action plan
3-month time point	*Local action plan*: Knowledge broker will review and update the local action plan for each RACF (including reflection on successes and challenges in previous quarter) and present to RACF management team, Medication Advisory Committee and Project Management Team
	*QUM service*: Delivery of second QUM service according to group allocations
	*Intervention*: Ongoing delivery of knowledge broker services as per local action plan Support and evaluation: Engagement in semi-structured interviews and focus groups
6-month time point	*Local action plan*: Knowledge broker will review and update the local action plan for each RACF (including reflection on successes and challenges in previous quarter) and present to RACF management team, Medication Advisory Committee and Project Management Team
	*QUM service*: Delivery of third QUM service according to group allocations
	*Intervention*: Ongoing delivery of knowledge broker services as per local action plan *Support and evaluation*: Engagement in semi-structured interviews and focus groups
9-month time point	*Local action plan*: Knowledge broker will review and update the local action plan for each RACF (including reflection on successes and challenges in previous quarter) and present to RACF management team, Medication Advisory Committee and Project Management Team
	*QUM service*: Delivery of fourth and final QUM service according to group allocations
	*Intervention*: Ongoing delivery of knowledge broker services as per local action plan *Support and evaluation*: Engagement in semi-structured interviews and focus groups
12-month time point	*Local action plan*: Knowledge broker will reflect on success and challenges for previous quarter
	*Study close-out*: Semi-structured interviews and focus groups with knowledge brokers

Abbreviations: *RACF*, residential aged care facility; *QUM*, quality use of medicine

Ongoing fidelity of the intervention delivered by the knowledge brokers will be monitored using the discussion boards, local action plans and monthly meetings with the Project Management Team. Meetings will mostly be conducted via video-teleconferencing (e.g. Zoom), with face-to-face meetings organised if needed.

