### Analysis plan

#### Effectiveness analysis

All primary analyses will be conducted using the intention-to-treat (ITT) principle. Level 3 intervention will be compared to level 1 and level 2 at the 6-month time point as a primary outcome (Table 4).

Per protocol analysis will also be undertaken with the per protocol set including all RACFs without a major protocol deviation. Major protocol deviations may include, but are not limited to, the following:Loss of knowledge brokerIncomplete delivery of intervention (e.g. local action plans, QUM service)

We anticipate that the primary analysis will be conducted using a linear mixed model treating the RACF as a random effect, with the strategy level and medication contexts as fixed effects. Multiple imputation will be used to impute missing covariate values where necessary. Data will be analysed using Stata/SE Statistical Software: Release 17.0 (StataCorp. 2021).

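### Months 9 and 12 are said to evaluate sustainability, but delivery runs for all 12 months and nothing is measured after it stops

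*Protocol article*

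**What the plan says.** All references are to the protocol article.

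- **Secondary outcomes:** "The 9- and 12-month time points will be used to evaluate intervention sustainability". The same sentence gives a second purpose, to pick up changes in policy and practice that had not appeared by 6 months. The Discussion presents the sustainability outcomes as evidence for policy.
- **Intervention:** "All three levels of implementation strategies will be delivered simultaneously throughout the 12-month intervention period at the RACF-level". Each level contains the activities of the level below it.
- **Level 2:** "The pharmacist will deliver a QUM service once per quarter, with a total of four QUM services delivered over the 12 months".
- **Table 3 (Level 3):** sessions fall at baseline, 3, 6 and 9 months. The 9-month row reads "Delivery of fourth and final QUM service according to group allocations" and also lists broker services as continuing. The 12-month row asks the broker to reflect on the quarter just ended and closes the study.
- **Data collection and Table 4:** data are taken at baseline, 3, 6, 9 and 12 months. Table 4 marks the intervention as being implemented at each of these points, month 12 included.
- **Primary outcome:** "This outcome will be measured at the 6-month time point, informed by a similar study conducted in RACFs". The Effectiveness analysis section compares level 3 with levels 1 and 2 at that point.

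**The concern.** Sustainability of an implementation strategy is ordinarily read as whether practice holds once the support is taken away. To observe that, at least one measurement must follow the end of delivery. The schedule appears to have none.

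What is at stake is the conclusion drawn from the later results. If the level 3 advantage seen at 6 months is still there at 12 months, the stated purpose invites the report that it was sustained. A funder deciding whether a broker is needed for a limited period or indefinitely could take that as evidence for a limited period. The data would only show that the advantage lasts while a broker is in post.

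**Working it through.** **1. Delivery and measurement side by side** (Tables 3 and 4, Intervention, Data collection)

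| Month | Education session | Broker service (level 3) | Data collected | Delivery time left (12 − month) |
|---|---|---|---|---|
| 0 | 1st | starts | yes | 12 |
| 3 | 2nd | continuing | yes | 9 |
| 6 | 3rd | continuing | yes (primary) | 6 |
| 9 | 4th, last | continuing | yes | 3 |
| 12 | none | end of delivery period | yes, last | 0 |

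The table shows 4 sessions, which agrees with the total given under Level 2.

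**2. Follow-up after delivery.** Last data collection minus end of delivery is 12 − 12 = 0 months. At month 9 there are still 12 − 9 = 3 months of delivery to run. Every facility receives all three levels, each for a different drug class, for the whole period. No level is withdrawn from any facility during the trial, so no off-intervention contrast can be formed within it either.

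**3. Education considered alone.** Month 12 is 12 − 9 = 3 months after the last session. The gap between consecutive sessions is also 3 months (3 − 0, 6 − 3, 9 − 6). Month 12 is therefore no further from a session than facilities ordinarily are just before the next one. For level 3, the broker service covers that last quarter too.

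**4. Education delivered at the primary time point.**

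- Sessions strictly before month 6: 2 of 4 = 50%, leaving 50% to come.
- Sessions at or before month 6: 3 of 4 = 75%, leaving 25% to come.

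Table 3 does not say whether the third session comes before or after the 6-month data collection, so the share still to come lies between 25% and 50%. It is the same for levels 2 and 3, because level 3 includes the level 2 activities.

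**The case against.** The sustainability sentence has a second half. Looking for change that had not occurred by 6 months is a sound use of the later time points, and the schedule supports it. That stands, and that purpose should be kept. It describes a later effect under delivery, however, and does not rescue the first half.

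It can also be said that the last education session is at month 9 and that Table 3 lists only reflection and close-out at month 12, so month 12 gives some view of education after it ends. This has limited force. The interval is only the usual gap between sessions, the Intervention section keeps all levels running to month 12, and the broker service, which is the strategy under test, is not withdrawn in that quarter.

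A reader might infer something stronger: that 6 months is too early, that level 2 is scored on content not yet taught, and that power is lost as a result. The document does not support this.

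- Two or three of the four sessions have been given by month 6, so it is wrong to say that less than half has been delivered.
- The text says "The four sessions will cover the Guidelines, initiation, adverse events and monitoring and discontinuation", but Table 3 numbers the sessions without naming topics. Which topic falls when is inferred from the order of a list.
- The Guidelines and fact sheets are handed out at baseline under every level, and concordance results are fed back each quarter, so staff are not unexposed to monitoring and tapering content.
- The 6-month choice has a stated rationale, in a cited study that is not available here.
- The 5-point effect for level 2 against level 1 was set for the primary outcome, which is the 6-month outcome. Discounting it for incomplete delivery would count the same thing twice. That contrast is also not one of the two named as primary in the Effectiveness analysis section.

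**Conclusion.** The point holds for the word sustainability and the claim attached to it. The design has zero months of follow-up after delivery ends, so the 9- and 12-month results cannot show persistence without the broker. They can show whether an effect continues, grows or appears late while delivery continues.

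The primary outcome, its time point and its analysis are unaffected. That 25% to 50% of the education sessions remain at 6 months is a matter of interpretation for the level 2 and level 3 results. It is not an error and gives no basis for revising the power statement.

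The conclusion rests on taking the Intervention section and Table 4 at their word that delivery lasts to month 12, and on there being no later data collection than the one the article lists.

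**What to change.** - In Secondary outcomes, replace sustainability with *longer-term effect during continued delivery* as the purpose of the 9- and 12-month time points. Keep the purpose of capturing change not seen by 6 months.
- Make the same replacement in the Discussion, and state that the trial makes no claim about persistence after the intervention ends.
- Add one interpretive sentence: at the 6-month primary time point one or two of the four QUM sessions are still to be delivered, so the level 2 and level 3 results describe a part-delivered education programme. Say whether the third session comes before or after the 6-month data collection.

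The cost is a few words and the loss of a claim that the data could not have supported. The schedule, session order, primary time point and sample size need no change. If persistence is a question the investigators want answered, it would need a data collection after delivery has stopped, which is an addition to the trial and not a correction of the text.
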